### 2.7. Non-Inferiority Margin Settings

Initially, we would apply the fixed-margin method recommended by the Food and Drug Administration; however, there is insufficient data to estimate the risk ratio of standard intervention [26]. The European Medicines Agency [27] has indicated that “In such situations, it will be difficult to specify delta using the considerations outlined above; however, the best efforts should still be made to produce an indirect confidence interval for the new product against placebo using whatever data exist for the reference.” From this regulator’s view, it is best to consider delta somehow by using indirect data when studying treatments with no evidence of comparison to a placebo. Therefore, we decided to apply a method of determining margins based on scientific theory.

The risk ratio is superior to the risk difference in terms of robustness to differences in rates of outcome between previous studies and non-inferiority studies [28]. In addition, the risk difference is considered an index when analysing binary categorical data. Since the risk ratio is commonly used when performing a time-to-event analysis, the non-inferiority margin was set, based on the risk ratio.Estimating the risk ratio of standard intervention:

Since there is no placebo comparison of either 5% sodium carbonate or dimeticone, we will estimate whether the treatment group shows the same results as those reported by [29].2.Setting the risk difference of standard intervention using the lower limit of the effect estimate:

95%CI: −0.563 to −0.299.3.Setting the retention rate and calculating the non-inferiority margin (Wangge et al. [30]):

1 − ε = 0.67

Δ = (1 − 0.67) × −0.299 = −0.09867.

4.Range of interpretation: ±10%.

### 2.8. Sample-Size Calculation

Based on the hypothesis, there is a difference between treatment with 5% sodium carbonate, with a 70% cure rate [14], and dimeticone, with a 78% cure rate [15]. Although it depends on the result of the pilot study, we would like to calculate the sample size assuming that both cure rates are 80%. The sample size was calculated using the method proposed by Schoenfeld [31], assuming a non-inferiority margin of 10% (δ = 0.1) and that the true mean cure-rates of the treatment agent (sodium carbonate) and the active control (NYDA^®^) are 80% (pT = 0.80) and 80% (pC = 0.80), respectively. We calculate the optimum sample needed to achieve 90% power (1 − β = 0.9) at the 5% level of significance (α = 0.05) with equal allocation (*k* = 1) for demonstrating non-inferiority for the clinical-cure assessment of efficacy. Since one to five lesions per foot will be studied per participant, the intra-class correlation coefficient (ICC) (1, *k*) with *k* = 2–5, would be used to evaluate the intra-rater reliability of the values, yielding an estimated ICC = 0.5. As the cluster size is two, the design effect is calculated as 1 + (2 − 1) × 0.5 = 1.5. A total of 920 (460 per arm) lesions will be recruited, considering a 10% rate of loss to follow-up. 

Before conducting this non-inferiority trial, a cohort study will be conducted as a pre-study. The sample size is estimated to have an 80% efficacy rate, absolute precision is 10%, and therefore 62 lesions are enrolled in each concurrent, parallel-treatment cohort.

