**Hypothesis:** 
*In this study, we hypothesise that the topical risk-difference of 5% sodium carbonate is no more than 10% non-inferior to dimeticone (NYDA^®^) when used in the treatment of tungiasis.*

Figure 1 shows the non-inferiority margin and the relationship with 95% confidence interval (95% CI) of the difference between experimental and control groups. If the risk difference of cure rate (95%CI) is greater than −10%, it can be shown than 5% sodium carbonate is not inferior to NYDA^®^.

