### 4.1. Statistical Analysis

For the primary outcome, logistic regression analysis (stepwise regression) will be performed, because it is binary. Since all secondary outcomes are score data, they are continuous measures; thus, analysis of covariance will be performed using two variables (sex (male or female) and footwear use (shoes or sandals)) as covariants. This is because previous studies have shown that the male sex is a risk factor for tungiasis, and that the thickness of the skin of the foot may change depending on whether sandals are used, which may affect the penetration of the treatment [32]. We will use generalized estimating equations for side effects such as pain and itching, to consider relative risks. The per-protocol set, which analyses only subjects who adhere to treatment, is more likely to show superiority or a significant increase in risk, while the intention-to-treat analysis is more likely to show non-inferiority with or without significant differences. Therefore, a per-protocol approach will be adopted for this non-inferiority study. All data will be analysed using EZR version 1.60 (Jichi Medical University Saitama Medical Center, Saitama, Japan). Missing values will be imputed using the multiple-imputation method. For the main analysis, we will use one-sided *p*-values at an *α* = 0.025 level of significance; for others, we will use two-sided *p*-values at an *α* = 0.05 level of significance.

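### The 460 lesions per arm were sized at a one-sided 5% level, but the primary test is one-sided 2.5%, so on the plan's own inputs power is about 84%, not 90%

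*Protocol article*

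**What the plan says.** Three places in the protocol article fix a significance level for the same comparison.

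- **Section 2.8 (Sample-Size Calculation)** gives the size "needed to achieve 90% power (1 − β = 0.9) at the 5% level of significance (α = 0.05"). It does not say whether the 0.05 is one-sided or two-sided. The other inputs are in the same section: the calculation is made "assuming a non-inferiority margin of 10% (δ = 0.1"), the true cure rates "are 80% (pT = 0.80) and 80% (pC = 0.80), respectively", the arms are equal in size, the design effect is 1.5 and loss to follow-up is 10%. The result is 460 lesions per arm, 920 in all.
- **Section 4.1 (Statistical Analysis)** states: "For the main analysis, we will use one-sided *p*-values at an *α* = 0.025 level of significance".
- **The Hypothesis statement** at the end of the Introduction sets the decision rule: "If the risk difference of cure rate (95%CI) is greater than −10"%, sodium carbonate is declared non-inferior.

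**The concern.** A two-sided 95% confidence interval compared with a margin is a one-sided test at 0.025. The Hypothesis statement and Section 4.1 therefore agree, and Section 2.8 is the one that may differ. If its 0.05 is two-sided, all three places agree and nothing is wrong. If it is one-sided, the trial was sized for a more lenient test than the one it will run, and the 90% power belongs to a test nobody will perform.

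The 90% figure is the stated justification for recruiting 920 lesions in children. If the true power is lower, the trial is more likely to end inconclusively even when the two treatments are equally effective. Two levels in one document also leave room for a borderline result to be read at the looser one.

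**Working it through.** **Inputs (all Section 2.8 except the test level).** Cure rates pT = pC = 0.80; margin δ = 0.10; power 0.90; equal allocation; design effect 1 + (2 − 1) × 0.5 = 1.5; loss 10%. Test level: one-sided 0.025 (Section 4.1).

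**Formula.** The usual unpooled normal approximation for a risk difference, per arm:

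n = (z₁₋α + z₁₋β)² × [pT(1 − pT) + pC(1 − pC)] / δ²

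The variance term is 0.16 + 0.16 = 0.32, and 0.32 / 0.10² = 32. The result is multiplied by 1.5 for clustering and divided by 0.9 for loss.

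**Step 1: which level gives 460?**

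| Level | (z₁₋α + z₁₋β)² × 32 | × 1.5 | ÷ 0.9 |
|---|---|---|---|
| One-sided 0.05 | (1.645 + 1.282)² × 32 = 274.0 | 411.1 | 456.7 |
| One-sided 0.025 (= two-sided 0.05) | (1.960 + 1.282)² × 32 = 336.2 | 504.4 | 560.4 |

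Rounding up to whole lesions at the first step gives 459 and 562. The plan's 460 is reproduced at one-sided 0.05 and is about 100 per arm short at one-sided 0.025.

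**Step 2: could another formula give 460 at one-sided 0.025?**

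- Allowing for loss by multiplying by 1.1 instead of dividing by 0.9: 557 (454 at one-sided 0.05).
- Farrington–Manning variance: 566 (461 at one-sided 0.05).
- Continuity correction: 595 (491 at one-sided 0.05).
- Margin 0.09867 from Section 2.7 in place of 0.10: 577 (470 at one-sided 0.05).
- No design effect: 375, or 396 with the continuity correction.
- Design effect kept, no allowance for loss: 504.

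None of these comes near 460. Reading the 0.05 in Section 2.8 as two-sided therefore does not fit the plan's own result.

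**Step 3: power of 460 per arm.** Evaluable lesions per arm: 460 × 0.9 = 414. Effective number: 414 / 1.5 = 276.

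Power = Φ( √(276 × 0.10² / 0.32) − z₁₋α ) = Φ(2.937 − z₁₋α)

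- One-sided 0.05: Φ(2.937 − 1.645) = 0.902, the plan's 90%.
- One-sided 0.025: Φ(2.937 − 1.960) = 0.836.

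If no lesion is lost, the effective number is 460 / 1.5 = 306.7 and power at one-sided 0.025 is 0.872, still below 90%.

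**The case against.** The strongest objection is that 84% is not the trial's real power. Every child receives both treatments, one per foot (Sections 2.3 and 3.2), so the comparison is within child. With one lesion per foot and a between-foot correlation of 0.5, the variance factor would be 1 − 0.5 = 0.5 instead of 1.5. The effective number would be 414 / 0.5 = 828 and power about 99.9%. With five lesions per foot, a within-foot correlation of 0.5 and little correlation between feet, the factor would be 1 + (5 − 1) × 0.5 = 3, the effective number 138 and power about 55%. The primary analysis in Section 4.1 is also a stepwise logistic regression, not the simple risk-difference test used here. This stands as a limit on what 84% means. It does not restore 90% on the plan's inputs, because Section 2.8 itself chose 1.5. Whether 1.5 is suitable is a separate question.

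Second, the one-sided reading is inferred. Section 2.8 cites a published method that is not at hand, and 456.7 is not exactly 460. That is fair, but the gap is of rounding size at one-sided 0.05 and about 100 lesions per arm at one-sided 0.025.

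Third, the error is in the safe direction. The decision rule keeps its 2.5% level, so this mismatch does not raise the risk of a false non-inferiority claim. Section 2.8 also makes the cure rates provisional on the pre-study. Both points are true. The first limits the harm to lost power. The second allows a recalculation of the rates, but nothing in the text corrects the level.

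**Conclusion.** The concern holds. On its own inputs the plan sized the trial at one-sided 0.05 and will test it at one-sided 0.025. At the planned test, 460 lesions per arm give 83.6% power, a shortfall of about 6 points. With no true difference between treatments, the trial would miss non-inferiority about one time in six instead of one in ten. Holding 90% would take about 560 per arm, roughly 100 more.

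The figures assume 80% cure in both arms, a design effect of 1.5, 10% loss and a normal approximation for the risk difference. They also take the 95% interval in the Hypothesis statement as two-sided, which its agreement with Section 4.1 supports.

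**What to change.** In Section 2.8, state the level as one-sided 0.025, so that it matches Section 4.1 and the 95% confidence interval rule. Then take one of two courses:

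- **Keep 920 lesions** and restate the power as about 84% under the stated cure rates, margin, design effect and loss. This costs only wording and a less favourable figure.
- **Keep the 90% claim** and raise the size to about 560 per arm (560.4 before rounding; 562 if rounded up first), about 1,120 in all. This means recruiting about 200 more lesions.

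The level of the primary test should stay at one-sided 0.025. If the design effect or the cure rates are revised, for example after the pre-study, the calculation should be rerun at that level.

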### 2.3. Study Design

The study will utilise a randomised design, compared to standard treatment intervention. Figure 3 shows the flowchart of this study. It will have two arms: treatment of embedded sand-flea infestations with 5% sodium carbonate, versus dimeticone. Randomisation will be performed according to treatment. A non-inferiority design is chosen, since it would be unethical to withhold an existing treatment that has demonstrated efficacy. This study will not measure any environmental intervention; therefore, we can measure only efficacy, not effectiveness. All participants will receive both treatments, one on each foot. Therefore, it is not possible to blind participants and interveners to treatment-group assignments. The study will be conducted during the dry season, when the prevalence of tungiasis is known to be at its peak, and at a time not impacted by holidays.

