#### 2.5.1. Eligibility Criteria

Children aged 8 to 14 years who have been infected with tungiasis in Homa Bay, Kenya (the most commonly affected age-group, and who can reliably answer questions).Children and caregivers who provide written assent and consent to participate in the study.Children who have more than one lesion of embedded sand-fleas that are independent (not clustered) and easily observable, on both feet.

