We will sample participants with a smaller number of lesions sides, and select one to five embedded sand-fleas per foot. Because it is difficult to distinguish the characteristics of individual lesions [15], we will limit the number of lesions studied. The growth level of the target lesions should be stage II or III, according to the Fortaleza classification [2]. Only lesions that can be clearly distinguished from one another with viable embedded sand-fleas will be included in the study. Lesions will be chosen such that their location will make it possible to use a handheld digital microscope. Each lesion will be photographed and circled with a marker, and its location and stage noted in the patient’s record.

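### The design effect of 1.5 does not match the split-foot, multi-lesion design, so the 90% power for 460 lesions per arm is unsupported, in a direction the protocol does not settle

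*Protocol article*

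**What the plan says.** Section 2.8 assumes 80% cure in both arms, a margin of 10 percentage points, 90% power, alpha 0.05 and equal allocation. It notes that one to five lesions per foot will be studied, then introduces an ICC(1, k) with k = 2–5 which "would be used to evaluate the intra-rater reliability of the values, yielding an estimated ICC = 0.5". The inflation follows: "As the cluster size is two, the design effect is calculated as 1 + (2 − 1) × 0.5 = 1.5". The result, after allowing for 10% loss to follow-up, is 920 lesions, 460 per arm.

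Three other places describe the data that this factor has to represent:

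- Section 3.1, Stage 4: the team will "select one to five embedded sand-fleas per foot".
- Section 2.5.1 admits "Children who have more than one lesion of embedded sand-fleas that are independent (not clustered) and easily observable, on both feet".
- Section 2.3: "All participants will receive both treatments, one on each foot". The envelopes in section 3.1 randomise which foot gets which treatment.

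**The concern.** The factor departs from the design in three ways.

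1. **The ICC.** Intra-rater reliability says how repeatable an observer's readings are. A design effect needs the correlation of cure between lesions on the same foot, and between lesions on the two feet of one child. The protocol gives neither.
2. **The cluster size.** No mean lesion count is stated that would lead from one to five per foot to two.
3. **The formula.** 1 + (m − 1)ρ applies when every member of a cluster is in the same arm. Here each child contributes to both arms, and positive correlation between the feet reduces the variance of the treatment difference.

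The 920 lesions and the 90% power both rest on this factor. If it is wrong, the trial may be too small to show non-inferiority or may enrol more children than it needs.

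**Working it through.** **Reproducing the stated figure.** Inputs from section 2.8: p = 0.80 in both arms, δ = 0.10, power 90%, alpha 0.05 (sidedness not stated), design effect (DE) 1.5, loss 10%.

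For independent lesions, n per arm = (z_α + z_β)² × 2p(1 − p)/δ². At one-sided 0.05 this is (1.645 + 1.282)² × 0.32/0.01 ≈ 274.1, rounded up to 275. Then 275 × 1.5 = 412.5, and 412.5/0.9 = 458.3, rounded up to 459, against 460 stated. At one-sided 0.025 the chain is 337, 505.5 and 562, which does not match. The 460 therefore comes from one-sided 0.05, and the multiplication is correct.

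**What "As the cluster size is two, the design effect is calculated as 1 + (2 − 1) × 0.5 = 1.5" can mean.**

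- *Two is the two feet of a child.* The feet are in opposite arms, so the correlation enters with a minus sign: 1 − 0.5 = 0.5, not 1.5. The need would be 275 × 0.5/0.9 = 152.8, or 153 per arm.
- *Two is two lesions on one foot.* Then 1.5 holds only for exactly two lesions per foot, a correlation of cure of 0.5 and no correlation between the feet. Other combinations reach 1.5 by coincidence, for example m = 4 with ρ_within = 0.5 and ρ_between = 0.25: 1 + 1.5 − 1 = 1.5.

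Treating the 0.5 as a mislabelled lesion ICC does not settle it. ICC(1, k) refers to an average of k values. The single-value ICC it implies is 0.5/[k − (k − 1) × 0.5], which is 0.33 at k = 2 and 0.17 at k = 5.

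**A factor that fits the design.** With m lesions on each foot, the variance of the difference in cure proportions is [2p(1 − p)/n] × DE, where n is lesions per arm and

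DE = 1 + (m − 1)ρ_within − mρ_between.

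**Range.** Evaluable lesions per arm: 460 × 0.9 = 414. Assumptions, because the protocol gives no values: ρ_within = 0.5 (the protocol's number, borrowed), ρ_between = 0, 0.25 or 0.5, and equal m on every foot. Alpha is kept at one-sided 0.05 so that only the design effect changes. Power = Φ(√(414/DE × 0.01/0.32) − 1.645). Lesions to recruit per arm for 90% power = 275 × DE/0.9.

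| Lesions per foot | ρ_between | DE | Power with 414 evaluable | Recruit per arm for 90% |
|---|---|---|---|---|
| 2 | 0 | 1.5 | 90% | 459 |
| 3 | 0 | 2.0 | 82% | 612 |
| 5 | 0 | 3.0 | 67% | 917 |
| 2 | 0.25 | 1.0 | 97% | 306 |
| 3 | 0.25 | 1.25 | 94% | 382 |
| 5 | 0.25 | 1.75 | 86% | 535 |
| any | 0.5 | 0.5 | above 99% | 153 |

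With one lesion per foot, DE = 1 − ρ_between. That is at most 1 when the feet are not negatively correlated, so 1.5 is conservative there. Unequal lesion counts between feet would push DE up.

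**Children.** 460 lesions per arm is 460 children at one lesion per foot, 230 at two and 92 at five. Section 2.8 states only lesions.

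**The case against.** Much can be said for the protocol.

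- Its arithmetic is right. The dispute is over an assumption.
- Two is a possible mean of a one-to-five range, and no document shows that 0.5 is the wrong value for correlation of cure. These two inputs are unexplained rather than proved false.
- Leaving out a positive between-feet correlation, taken alone, makes the trial larger than needed, which is the safe side.
- The 67% figure needs five lesions on every foot and no correlation between the feet of one child. The documents support neither, and section 3.1 limits the number of lesions studied.
- The savings at high between-feet correlation come only with an analysis that uses the pairing. Section 4.1 names stepwise logistic regression for the primary outcome and mentions generalized estimating equations only for side effects.

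All of this stands, and it limits the point to an unsupported variance. Three stronger readings are tempting and do not hold:

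- *The trial is underpowered.* A reader might infer this from the upper rows of the table, but the lower rows point the other way and the documents do not choose between them.
- *Two lesions per foot is the minimum, so 1.5 is a floor.* Sections 2.8 and 3.1 both allow one lesion per foot. The eligibility wording in section 2.5.1 can be read as more than one lesion in total, spread over both feet.
- *Power is already down to 84%.* That figure appears if 414 lesions with the unchanged factor of 1.5 are tested at the level in section 4.1: "For the main analysis, we will use one-sided *p*-values at an *α* = 0.025 level of significance". The loss then comes wholly from the conflict with section 2.8, which works "at the 5% level of significance (α = 0.05) with equal allocation". It is a separate issue.

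The objection does not rescue the formula. On neither reading of two does it represent a comparison in which every child supplies both arms and lesion counts vary from one to five.

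**Conclusion.** The concern holds as a fault in the variance model. The factor of 1.5 rests on a correlation of the wrong kind, an unexplained cluster size and a formula for a different design, so the 90% power claim for 460 lesions per arm has no support in the protocol. Over 2 to 5 lesions per foot, with an assumed within-foot correlation of 0.5 and between-feet correlation from 0 to 0.5, the design effect runs from 0.5 to 3.0. The requirement then runs from about 153 to 917 lesions per arm at one-sided 0.05. These limits depend on assumed correlations and equal lesion counts, and the low end also needs a paired analysis. Whether 460 is too few or too many cannot be told from the document.

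This is not detail left to an analysis plan or lost in condensing the article: the formula, its inputs and its result are all stated.

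**What to change.** 1. In section 2.8, replace the factor with 1 + (m − 1)ρ_within − mρ_between. Define both correlations as correlations of cure, give the expected mean number of lesions per foot, and drop the reliability ICC from the calculation.
2. Restate power as a range over plausible correlations and lesion counts, and give the number of children as well as lesions.
3. Specify a primary analysis that accounts for clustering and pairing by child, so that the assumed variance is the one the analysis delivers.
4. Use the pre-study to inform the correlations only if it is split-foot. Section 2.8 describes concurrent parallel cohorts, while section 3.6 says the method is that of the main trial. The two must be reconciled, because cohorts of different children give no between-feet correlation. Even if it is split-foot, 124 lesions will estimate two correlations imprecisely, so the range in step 2 is still needed.
5. Make the eligibility wording on lesion count (section 2.5.1) agree with the one-to-five rule (section 3.1).

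The cost is a recalculation and some redrafting, with no new data beyond the planned pre-study. The downside is that the restated power may be less favourable than 90%.

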## 3. Procedure

### 3.1. Sampling and Recruitment

A multi-stage sampling method will be used in this study. Stage 1 will involve the sampling of sub-counties, stage 2 will involve the sampling of schools, participant selection will be performed in stage 3, and stage 4 will involve the sampling of embedded sand-fleas.

Stage 1: Sampling of sub-counties:

Ndhiwa and Suba South sub-counties will be sampled because they have the highest number of reported cases of tungiasis in Homa Bay County. 

Stage 2: Sampling of schools:

Primary schools in the study area are ranked according to the number of reports made to the Health Department. Therefore, we will visit schools in areas with the highest number of reported cases and with the highest number of affected students, in order. 

Stage 3: Sampling of participants:

In each school, children aged 8 to 14 years will be selected in descending order of grade. At the beginning of the study, a sealed envelope will be used to randomise the two treatments. In the sealed envelopes will be written “Right foot: dimeticone, Left foot: 5% sodium carbonate” or “Right foot: 5% sodium carbonate, Left foot: dimeticone” with a participant number. Before randomisation, lesions will be sampled to avoid selection bias.

Children will be informed not to manipulate the lesions during the next 7 days. Children whose skin conditions are suspected to be due to tungiasis by teachers, caregivers, and healthcare workers (including community health-volunteers) will be screened for eligibility to participate in this study. Such children and their caregivers will then be contacted by the local co-investigator and their field assistants to ask if they are willing to participate in the study, after explaining the study objectives and procedures. Informed consent from caregivers and assent from children will be obtained after both agree to participate. Participants will be randomly selected until the point of saturation is reached.

Stage 4: Sampling of embedded sand-fleas:

We will sample participants with a smaller number of lesions sides, and select one to five embedded sand-fleas per foot. Because it is difficult to distinguish the characteristics of individual lesions [15], we will limit the number of lesions studied. The growth level of the target lesions should be stage II or III, according to the Fortaleza classification [2]. Only lesions that can be clearly distinguished from one another with viable embedded sand-fleas will be included in the study. Lesions will be chosen such that their location will make it possible to use a handheld digital microscope. Each lesion will be photographed and circled with a marker, and its location and stage noted in the patient’s record.

